**Severe pre-eclampsia refers to a pregnant woman with one of the following symptoms:**

1) Uncontrolled blood pressure: systolic blood pressure ≥160mmHg and/or diastolic blood pressure ≥110mmHg;

2) Persistent headache, visual disturbance, or other central nervous system abnormalities;

3) Persistent upper abdominal pain, subcapsular hematoma or liver rupture;

4) Elevated serum alanine aminotransferase (ALT) or aspartate aminotransferase (AST) levels;

5) Impaired renal function: urinary protein content > 2.0g/24h; oliguria (24h urine volume < 400ml, or < 17ml/hour), or serum creatinine level > 106μmol/L;

6) Hypoproteinemia with ascites, pleural effusion or pericardial effusion;

7) Platelet count decreased and lower than 100×10^9^/L; hemolysis, anemia, elevated lactate dehydrogenase (LDH), or jaundice;

8) Heart failure;

9) Pulmonary edema;

10) Fetal growth restriction or oligohydramnios, fetal death, placental abruption, etc.

**End events**

1) Termination of pregnancy

2) The following conditions occur: vaginal bleeding, regular and painful contractions, premature rupture of membranes, dyspnea, dizziness, headache, chest pain, muscle weakness affecting balance

3) Other serious clinical diseases which are not suitable for further study.

**Grouping scheme**

1. Grouping method: During early pregnancy (11~13+6 weeks), an ActiGraph wGT3X-BT exercise accelerometer will be worn on the wrist to monitor the intensity, time, number of steps and energy metabolism of daily physical activity within 1 week, and the number of exercise steps will be collected by mobile phone APP. Participants will be divided into light and moderate groups according to the activity intensity of early pregnancy. Moderate-intensity activity is defined as 150 minutes per week, and the light-intensity activity group has a activity intensity or activity time of fewer than 150 minutes per week.

2. Drug intervention plan: pregnant women in both groups take low-dose aspirin 100mg daily from 11 to 13+6 gestational weeks until 2 to 7 days before termination or 34 gestational weeks as recommended by the guidelines. Oral calcium supplementation should be at least 1 g/ day.

3. Health guidance: limit salt intake (<6 g/d), smoking cessation, regular rest, weight control, etc.

4. Exercise monitoring: Wear an ActiGraph wGT3X-BT exercise accelerometer on wrist to monitor physical activity for a week. Except for bathing, swimming and other contacts with water, the rest of the time should be worn as required, ensure that more than 10 hours of wear every day, and at least two working days (Monday to Friday), rest day (Saturday to Sunday) with one day of valid data.

1) Activity intensity: light physical activity (100 -1952 CPM) and moderate physical activity (≥1952 CPM). Data were collected by ActiLife 6.0 analysis software after completion.

2) Active metabolic rate: measured by average metabolic equivalents (METs).

3) Perceived exertion rating: ratings of perceived exertion (RPE) based on the Borg perceived Exertion Scale (Table 1) are used. The Borg scale has 15 ratings ranging from 6 to 20, representing different levels of fatigue, with 6 being "very, very easy" and 20 beings "very, very difficult". For moderate-intensity exercise, the RPE score of pregnant women should be 13 to 14 points, that is, the feeling of self-exercise intensity is somewhat difficult.

[figure not shown]

**Outcomes**

1. Primary outcome: the difference in 24-hour ambulatory systolic blood pressure change from baseline during the third trimesters of pregnancy;

2. Secondary outcomes: the difference in 24-hour ambulatory systolic blood pressure change from baseline during the second trimesters of pregnancy; the difference of daytime and nighttime ambulatory blood pressure, daytime and nighttime and 24-hour diastolic blood pressure, and clinic blood pressure changes from baseline;

3. Exploratory outcomes: incidence of preeclampsia; effect of exercise on blood pressure control in pregnant women with preeclampsia

4. Safety outcomes: activity tolerance decline rate; incidence of shortness of breath; incidence of heart failure;

5. Other relevant outcomes: severe complications of preeclampsia (eclampsia, heart failure, pulmonary edema, HELLP syndrome, DIC), fetal death, iatrogenic premature delivery, neonatal asphyxia, NICU. Compliance with oral aspirin and calcium; mobile phone exercise recording monitoring exercise intensity compliance; the Subjective Exertion Scale (RPE) monitors an individual's exercise intensity tolerance.

[figure not shown]

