Chronic hypertension is estimated to affect 0.3% to 4.3% of pregnant women, and the risk of preeclampsia is 5.43 times in women with chronic hypertension than in those with normotensive. Furthermore, chronic hypertension was associated with a higher risk of cesarean section, maternal mortality, preterm birth, stillbirth, small for gestational age (SGA), low birth weight, and neonatal intensive unit admission [3, 4]. The abovementioned maternal and adverse perinatal outcomes are prone to occur in chronic hypertension-superimposed preeclampsia compared with preeclampsia alone [5, 6]. Blood pressure management is substantial throughout the perinatal period of pregnant women with chronic hypertension. Two large randomized trials [7, 8] found that antihypertensive treatment targeting a blood pressure <140/90 mmHg in chronic hypertension was safe and beneficial for maternal and neonatal. However, some agents should be avoided in pregnancy owing to the possible or proven concerns about fetotoxicity [9-11]. Pregnant women have limited options for antihypertensive medications compared with non-gestational. Pregnant termination should be considered to avoid maternal and fetal complications such as placental abruption and cardiovascular and cerebrovascular adverse events when hypertension is uncontrollable after active treatment. Lifestyle modifications can enhance the effects of antihypertensive therapy. Guidelines for gestational hypertension of pregnancy and non-gestational [12-14] had recommended lifestyle modifications, including salt reduction, smoking and alcohol cessation, healthy diet and drinking, weight reduction, and regular physical activity.

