**Method**

**Inclusion criteria**

Maternal age ≥ 18 years old, singleton pregnancy and fetal survival at 11^+0^ to 13^+6^ weeks of gestational age, history of chronic hypertension defined as hypertension diagnosed before pregnancy or at the first prenatal visit.

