2.7 Medication compliance

Take the medication prescribed by the doctor at each follow-up visit, and make statistics on the number of drugs taken.

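### The primary SBP comparison adjusts only for baseline blood pressure and does not address antihypertensive treatment, at baseline or later, in a non-randomised study of women with chronic hypertension

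*Supplement*

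**What the plan says.** The Supplement holds two protocols. This point concerns the later one, on daily physical activity and ambulatory blood pressure in chronic hypertension.

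- **Population (Inclusion criteria).** Women with a "history of chronic hypertension defined as hypertension diagnosed before pregnancy or at the first prenatal visit". Neither the inclusion nor the exclusion criteria require, restrict or exclude antihypertensive drugs.
- **Groups (Grouping scheme, item 1).** "Participants will be divided into light and moderate groups according to the activity intensity of early pregnancy". There is no randomisation.
- **Drugs set by the plan (Grouping scheme, item 2).** "Drug intervention plan: pregnant women in both groups take low-dose aspirin 100mg daily", and "Oral calcium supplementation should be at least 1 g/ day". Nothing else is named.
- **Primary outcome (Outcomes, item 1).** "the difference in 24-hour ambulatory systolic blood pressure change from baseline during the third trimesters of pregnancy".
- **Drug records.** The compliance outcome in Outcomes, item 5 names aspirin and calcium. Section 2.7 refers in general terms to medication prescribed by the doctor and asks staff to "make statistics on the number of drugs taken". The registration items (1.1 to 1.6) and the other follow-up items list no antihypertensive agent, dose, start or change.
- **Analysis (Statistical Analysis, Data analysis).** The primary outcome is analysed by ANCOVA with baseline blood pressure as the only covariate. The one sensitivity analysis is a per-protocol set, which is not defined by drug use.
- **Background.** Two trials are cited as showing that "antihypertensive treatment targeting a blood pressure <140/90 mmHg in chronic hypertension was safe and beneficial for maternal and neonatal". The same section states that "Lifestyle modifications can enhance the effects of antihypertensive therapy".

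**The concern.** Antihypertensive drugs act directly on the quantity that the primary outcome measures. The background acknowledges both that these women may be treated and that lifestyle interacts with treatment, but the design and analysis sections do not take this up.

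There are two separate routes to bias:

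1. **Before baseline.** The groups are self-formed, so the share of women on treatment may differ between them. Treated and untreated women with the same baseline pressure may follow different courses through pregnancy, and baseline blood pressure cannot tell them apart.
2. **After baseline.** Drugs may be started or increased during the second and third trimesters. A woman whose third-trimester SBP is low because a drug was added counts the same as one whose SBP stayed low without it. More escalation in the light group would shrink an activity effect. More in the moderate group would produce an apparent one.

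Without agent, dose and dates by group, the investigators could not say whether either had happened, in which direction, or by how much.

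**Working it through.** **Step 1: reproduce the plan's sample size.** Inputs from Data analysis: change of -7.3 (SD 12.7) mmHg with exercise and +1.1 (SD 8.2) in controls, two-sided alpha 0.05, power 90%, ratio 1, attrition 20%.

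- Difference: 1.1 - (-7.3) = 8.4 mmHg.
- Pooled SD: sqrt((12.7² + 8.2²)/2) = 10.69 mmHg.
- Two-sample t-test (noncentral t): 36 per group gives 90.8% power. The normal approximation gives 35.
- Attrition: 72/(1 - 0.20) = 90.

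The stated 36 per group, 72 in total and 90 recruited all reproduce. The sample-size arithmetic is not at fault.

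**Step 2: express differential drug change as a shift in SBP.**

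Net shift = (SBP effect of a start or escalation) × (difference between groups in the proportion started or escalated).

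The documents give neither factor. For illustration, assume an effect of 5 to 10 mmHg and a difference of 20 to 40 percentage points, which is about 7 to 14 women of 36 (0.20 × 36 = 7.2; 0.40 × 36 = 14.4):

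- 5 × 0.20 = 1 mmHg
- 10 × 0.20 = 2 mmHg, and likewise 5 × 0.40 = 2 mmHg
- 10 × 0.30 = 3 mmHg
- 10 × 0.40 = 4 mmHg

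**Step 3: consequences at 36 per group.** Standard error = sqrt((12.7² + 8.2²)/36) = 2.52 mmHg; noncentral t with 70 degrees of freedom. Masking takes a true effect of 8.4 mmHg less the shift. Mimicry takes no true effect, with the shift alone driving the difference.

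| Net shift (mmHg) | Difference left of 8.4 | Power (masking) | False-positive rate (mimicry) |
|---|---|---|---|
| 0 | 8.4 | 90.8% | 5.0% |
| 1 | 7.4 | 83% | 6.8% |
| 2 | 6.4 | 71% | 12% |
| 3 | 5.4 | 56% | 22% |
| 4 | 4.4 | 41% | 35% |

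These figures use the plan's own t-test framework and SDs, not the ANCOVA residual variance.

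**Step 4: does the baseline covariate deal with it?** No. Drug changes after the first-trimester recording are not in it. The baseline value is itself an on-treatment value for any woman already treated, so equal baseline pressures do not mean equal treatment.

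**The case against.** **Section 2.7 may already cover these drugs.** Its wording is not confined to aspirin and calcium, and Study quality control, item 5 keeps clinical and visit records as source documents. A reader might infer that the plan records no antihypertensive use at all; the text does not support that. What stands is narrower: Section 2.7 is a compliance count without class, dose or date, so as written it cannot show a start or an escalation. The retained records make the remedy cheap but do not replace a specified data item.

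**Measured SBP regardless of later drug changes is a legitimate target.** It is also what the ANCOVA estimates by default, since no drug-based exclusion is applied. A reader might infer that SBP change therefore tells us nothing about activity. That goes too far: under this estimand, later drug changes are part of the pathway being estimated and do not invalidate the analysis. But the plan does not state the estimand, its interpretation needs escalation by group, and the choice does nothing about confounding by baseline treatment.

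**The mechanism is inferred.** The protocol has no titration rule and no blood pressure target. The <140/90 mmHg figure describes other trials. A reader might infer that drugs will be raised to that target in this study, and more often in the light group; the documents say neither. They only leave such changes open, in either direction.

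**The size is assumed.** This objection stands in full.

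**Conclusion.** The point holds in a limited form. In a non-randomised comparison of women with chronic hypertension, the primary analysis adjusts for baseline blood pressure alone, and the plan neither specifies antihypertensive agent, dose and change dates as data items nor addresses them in the analysis. Baseline differences in use can confound the comparison. Differential starts or escalations can mask or mimic a direct activity effect.

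The bias cannot be quantified from the documents. Under assumed net shifts of 1 to 4 mmHg, power falls from 91% to between 83% and 41%, or the false-positive rate rises from 5% to between 7% and 35%. The mild end is modest. The severe end needs about 14 more women of 36 escalated in one group and a 10 mmHg drug effect, and nothing in the documents shows either to be likely.

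This should be changed because the remedy is specific and inexpensive. It does not show that the primary result would be uninterpretable.

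**What to change.** 1. At each of the three ambulatory monitoring points, abstract antihypertensive agent, dose and start or change dates from existing medical records.
2. Add baseline antihypertensive use (yes/no) as a covariate in the primary ANCOVA. This reduces confounding by baseline treatment but does not remove it, since a yes/no term ignores agent and dose. Drug use after baseline should not enter the primary model, because it may itself be a response to blood pressure.
3. State that the primary estimand is third-trimester change in 24-hour SBP regardless of later drug changes.
4. Report starts and escalations after baseline by group.
5. Pre-specify one sensitivity analysis for women started or escalated after baseline, for example adding back a range of values to their measured SBP, with those values labelled as assumptions.

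The cost is a few form fields, one model degree of freedom and one extra analysis. How the women are treated does not change.

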Exercise plays an important role in maintaining and improving cardiopulmonary function and reducing the risk of obesity, diabetes, hypertension and other chronic diseases at all stages of life. Pregnant women are also advised to maintain moderate exercise. Pregnancy exercise reduces joint edema, enhances physical strength during delivery, relieves pain, and reduces the incidence of cesarean section. Exercise during pregnancy also reduces depression. Moderate exercise during pregnancy does not increase premature birth and is helpful to control weight gain during pregnancy, reduce insulin resistance, and prevent gestational diabetes, preeclampsia and other pregnancy complications [15,16]. The consensus on exercise during pregnancy suggests that pregnant women without exercise contraindications should carry out moderate-intensity exercise lasting 30 minutes for 5 days every week [17]. Multiple guidelines have proposed that exercise during pregnancy could reduce the incidence of preeclampsia [17-21]. A meta-analysis showed that exercise reduced the risk of preeclampsia by 41% (OR 0.59, 95% CI 0.37 to 0.94) [15]. For pregnant women diagnosed with preeclampsia, preeclampsia is a contraindication for pregnancy exercise. However, the advantages and disadvantages of pregnancy exercise for such women need to be further confirmed. Further research is also needed to determine whether exercise interventions benefit blood pressure control in women with preeclampsia.

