**Exclusion criteria**

Severe cardiovascular or respiratory disease, hyperthyroidism, pregestational diabetes mellitus, incompetent cervix, recurrent spontaneous abortion, a history of spontaneous preterm birth, threatened abortion or inevitable abortion, placenta praevia, severe anemia, malnutrition or very low body weight (body mass index < 12kg/m2), with severe mental disorders and disable to express their will, with other obvious abnormal signs, laboratory examination and other clinical diseases.

**Diagnostic criteria** (2020 Chinese Guidelines for the Diagnosis and Treatment of Hypertensive Diseases during Pregnancy)

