**Data analysis**

The study is powered for the primary outcome measure of change in 24-hour ambulatory SBP from the first to the third trimester. The sample size calculation was based on the results of Lopes S et al.[14], who showed a decrease of -7.3 ± 12.7mmHg in 24-hour ambulatory SBP in the exercise group with 1.1 ± 8.2mmHg in the control group. A sample of 72 pregnant women (36 per group), with a two-sided significance level of 0.05, provided 90% statistical power to demonstrate this difference in 24-hour ambulatory SBP. In order to accommodate a 20% attrition rate, 90 pregnant women will be recruited (PASS11, independent t-tests; allocation ratio = 1).

Continuous variables will be presented as means ± standard deviations or median (interquartile range) according to normal distribution or not. Between-group differences at baseline will be tested with Student’s independent t-test or Mann–Whitney U test. For the categorical variables, results will be expressed as counts and percentages. Categorical variables will be tested with the chi-square test or Fischer test if appropriate between groups at baseline. The assessment of compliance with daily physical activity and safety will be summarized for the two groups. A cut-off of 80% of baseline physical activity during the second and third trimesters will be used to determine compliance well. Adverse events, if any, will be reported. The primary outcome and difference of the change in 24-hour ambulatory SBP from the first to the second trimester between groups will be analyzed using analysis of covariance, adjusting for baseline blood pressure. Other secondary outcomes will be analysis using general linear modelling to compare the difference of blood pressure change in the MPA and LPA groups at the second and third trimesters, adjusting for baseline blood pressure. The analyses will be conducted based on the intention-to-treat principle. The intention-to-treat population will comprise all the patients with the exception of those who do not complete ambulatory blood pressure measurement and physical activity monitoring at 3-time points for any reason, such as miscarriage, or preterm birth. Per-protocol set will be performed as a sensitivity analysis. Relative risks and 95% confidence intervals will also be provided. A two-sided p-value below 0.05 will be considered statistically significant in all analyses. Data will be analyzed using SPSS 25 statistical software.

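### Preterm birth is a named outcome only when iatrogenic, and spontaneous preterm birth, membrane rupture and miscarriage have no named outcome and can remove a woman from the analysis set

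*Supplement*

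**What the plan says.** All references are to the latest protocol in the Supplement, on pregnant women with chronic hypertension.

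- **Outcomes, item 5** (other relevant outcomes) names "fetal death, iatrogenic premature delivery, neonatal asphyxia, NICU". This is the only mention of preterm birth in the outcome list.
- **Outcomes, item 4** reads: "Safety outcomes: activity tolerance decline rate; incidence of shortness of breath; incidence of heart failure". It has no obstetric item.
- **Exclusion criteria** include "incompetent cervix, recurrent spontaneous abortion, a history of spontaneous preterm birth, threatened abortion or inevitable abortion".
- **End events, item 2** includes "vaginal bleeding, regular and painful contractions, premature rupture of membranes".
- **Data analysis** defines the intention-to-treat population as all women "with the exception of those who do not complete ambulatory blood pressure measurement and physical activity monitoring at 3-time points for any reason", and gives miscarriage and preterm birth as examples of such reasons. On harms it says only "Adverse events, if any, will be reported".
- **Background** states: "Moderate exercise during pregnancy does not increase premature birth". It also names preterm birth, without restriction to iatrogenic, among the risks of chronic hypertension, and calls for research on both the benefits and the harms of activity in these women.

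**The concern.** Background ties uncontrolled hypertension to termination of pregnancy, so iatrogenic preterm delivery is the type that better blood pressure control would be expected to reduce. Other preterm births, and losses not classed as fetal death, are the events a reader would want in order to judge harm, and they have no named outcome. They appear only as reasons for ending participation or for leaving the analysis set.

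The study could therefore finish without a by-group count of total preterm birth or total pregnancy loss. It could neither support nor question, in its own population, the Background statement that moderate exercise does not increase premature birth. An iatrogenic-only rate could also be read as the preterm rate when it is only part of it.

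**Working it through.** **1. Where each event appears in the text**

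| Event | Named outcome | Elsewhere |
|---|---|---|
| Iatrogenic preterm delivery | Yes, item 5 | Background |
| Spontaneous preterm birth | No | Exclusion (history); preterm birth of any type is a reason for removal in Data analysis |
| Membrane rupture | No | End events |
| Miscarriage | Unclear (fetal death is undefined) | Exclusion (threatened, inevitable or recurrent abortion); reason for removal in Data analysis |
| Fetal death | Yes, item 5 | Listed as a feature of severe preeclampsia |

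The follow-up data list (items 2.1 to 2.8) contains no gestational age at delivery, onset of labour or type of loss. Figures are not shown in the copy reviewed, so a schedule in a figure cannot be ruled out.

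**2. The plan's own design figure**

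Inputs from Data analysis: changes of −7.3 (SD 12.7) and +1.1 (SD 8.2) mmHg, a difference of 8.4; two-sided 0.05; 36 per group; 20% attrition.

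- SD = √((12.7² + 8.2²)/2) = 10.69.
- With 36 per group, the noncentral t gives power 0.908. With 35 it is 0.8998, so 36 is the first size to reach 90%.
- 72/0.8 = 90.

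The sample size reproduces. Nothing below changes it.

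**3. What an iatrogenic-only rate would show (assumed rates)**

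The documents give no preterm rates, so every risk here is an assumption. Take two competing causes with constant hazards, and let I and S be the iatrogenic and spontaneous risks in the light-activity group.

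- Total cumulative hazard H = −ln(1 − I − S); h_i = H·I/(I+S); h_s = H·S/(I+S).
- Multiply h_s by k in the moderate group. Total risk T′ = 1 − exp(−(h_i + k·h_s)); I′ = T′·h_i/(h_i + k·h_s); S′ = T′ − I′.

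*Case A: I = 20%, S = 6%, k = 2.* H = 0.3011, h_i = 0.2316, h_s = 0.0695. Then T′ = 1 − exp(−0.3706) = 31.0%, I′ = 19.4%, S′ = 11.6%.

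*Case B: I = 20%, S = 10%, k = 3.* H = 0.3567, h_i = 0.2378, h_s = 0.1189. Then T′ = 1 − exp(−0.5945) = 44.8%, I′ = 17.9%, S′ = 26.9%.

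| | Case A | Case B |
|---|---|---|
| All preterm, light to moderate | 26% to 31.0% (RR 1.19) | 30% to 44.8% (RR 1.49) |
| Iatrogenic, all enrolled women: I to I′ | 20% to 19.4% (RR 0.97) | 20% to 17.9% (RR 0.90) |
| Iatrogenic, spontaneous cases removed: I/(1−S) to I′/(1−S′) | 21.3% to 21.9% (RR 1.03) | 22.2% to 24.5% (RR 1.10) |

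Data analysis removes only women who miss a time point. If a fraction f of spontaneous cases is removed in both groups, the rates are I/(1 − fS) and I′/(1 − fS′). They are equal at f = (I − I′)/(I·S′ − I′·S), about 0.56 in case A and 0.58 in case B. Below that the iatrogenic rate falls; above it the rate rises. Iatrogenic deliveries before the last time point can be removed too, which leaves the direction open.

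**4. In women**

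Assume 45 per group (90/2; the plan groups by measured activity, so the real split may differ). In case A, iatrogenic deliveries move from 9.0 to 8.7 and spontaneous from 2.7 to 5.2. In case B, iatrogenic move from 9.0 to 8.1 and spontaneous from 4.5 to 12.1. If 4% to 10% of the 90 women delivered preterm spontaneously, 3.6 to 9 births would fall outside the named preterm outcome. Power at 45 per group is 14% for 5% versus 10%, and 35% for 5% versus 15%.

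**The case against.** **The events are not wholly invisible.** Adverse events are to be reported and staff are trained in reporting them. NICU and neonatal asphyxia are listed and can capture consequences of early birth, and fetal death may include miscarriage. This stands in part: the accurate statement is that these events have no named outcome, not that no one would record them. But the adverse-event sentence gives no list, definition or denominator. A late-preterm infant may need neither NICU nor resuscitation. None of these items separates spontaneous from iatrogenic birth.

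**A reader might infer that more spontaneous preterm birth would lower the reported rate and look like a benefit.** The documents do not support this. The fall needs every enrolled woman in the denominator, and Data analysis does not secure that. With the spontaneous cases removed the sign reverses. In case A the shift is 0.3 of one delivery in either description of benefit, too small to read as one.

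**A reader might also infer that the plan itself ties these harms to activity.** It does not say so. The exclusions and end events are general lists that also hold conditions such as hyperthyroidism, headache and dizziness, and Background denies an increase in premature birth. No exercise is assigned; women are grouped by measured activity.

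**Iatrogenic delivery is the pathway of interest and the sample is small.** Both are true. They justify keeping iatrogenic delivery as a category and making no formal test. They do not justify leaving out the other categories, since descriptive counts need no power.

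**Conclusion.** The gap is real and worth correcting. The latest protocol names preterm birth as an outcome only when iatrogenic. It names no outcome for spontaneous preterm birth or preterm membrane rupture, leaves miscarriage uncertain, and allows miscarriage and preterm birth to remove women from the analysis set. A rise in total preterm birth or loss could go unseen in the reported outcomes.

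On the assumed risks, total preterm birth rises by 5 to 15 percentage points while the iatrogenic-only rate moves by about 0.6 to 2.3 points, down or up according to the denominator. These figures rest on assumed base risks, constant hazards and a doubled or tripled spontaneous hazard. They illustrate the blind spot and do not predict an effect of activity. The wording of the outcome list and of the analysis set does not depend on them. The primary outcome and sample size are unaffected.

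**What to change.** 1. **Outcomes.** Replace iatrogenic premature delivery with preterm delivery from all causes (before 37 weeks), reported by type: spontaneous labour, preterm membrane rupture, iatrogenic. Replace fetal death with all pregnancy loss after registration, split into miscarriage and fetal death at a stated gestational cut-off. List both as safety outcomes.
2. **Data analysis.** State that these outcomes are reported descriptively by group in every enrolled woman, whether or not she completed the three time points or reached an end event. Without this sentence the change to Outcomes does not work, because the current set definition can remove the women concerned.
3. **Follow-up data registration.** Add gestational age at delivery or loss, onset of labour and type of loss, taken from the routine delivery or loss record.

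The cost is a few record fields and a wording change, with no new visit or procedure and no change to the 72 evaluable or 90 recruited. The reported preterm rate will be higher than an iatrogenic-only rate. With about 45 women per group the comparison remains descriptive.
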